#### **4.11.5 Deaths, Serious Adverse Events, and Other Significant Adverse Events**

A serious AE (SAE) is an AE that fulfils one or more of the following criteria:

- Results in death.
- It is immediately life-threatening.
- It requires inpatient hospitalization or prolongation of existing hospitalization.
- It results in persistent or significant disability or incapacity, or substantial disruption of the ability to conduct normal life functions.
- Is or results in a congenital abnormality or birth defect.

Other significant AEs are those reported as leading to an intervention e.g. withdrawal from study, discontinuation of study treatment, introduction of concomitant medication, dose reduction.

CRS is a systemic inflammatory response characterized by a spectrum of severity, ranging from flu-like symptoms (i.e., fever, myalgia, nausea/vomiting), to hypotension, respiratory and renal failure, and uncontrolled coagulopathy. The onset of CRS can typically occur between 24 hours and 14 days after the completion of T cell administration. Therefore, after agenT-797 infusion, should CRS occur, it should be managed by the Investigator per institutional guidelines.

The American Society for Transplantation and Cellular Therapy (ASTCT) have published consensus guidelines for grading of CRS ([Lee 2019](#)). The ASTCT consensus grading guidelines are presented in

[Table 3](#) and align with management algorithms developed by Lee and colleagues ([Riegler 2019](#)), which are to be used as a guide for the Investigator in the assessment of CRS.

**Table 3. ASTCT CRS Consensus Grading**

| Parameter          | Grade 1                               | Grade 2                                                  | Grade 3                                                                                       | Grade 4                                                                                |
|--------------------|---------------------------------------|----------------------------------------------------------|-----------------------------------------------------------------------------------------------|----------------------------------------------------------------------------------------|
| Fever*      | Temperature $\geq 38^{\circ}\text{C}$ | Temperature $\geq 38^{\circ}\text{C}$                    | Temperature $\geq 38^{\circ}\text{C}$                                                         | Temperature $\geq 38^{\circ}\text{C}$                                                  |
|                    |                                       | With                                              |                                                                                               |                                                                                        |
| Hypotension | None                                  | Not requiring vasopressors                               | Requiring a vasopressor with or without vasopressin                                           | Requiring multiple vasopressors (excluding vasopressin)                                |
|                    |                                       | And/or†                                |                                                                                               |                                                                                        |
| Hypoxia     | None                                  | Requiring low-flow nasal cannula ‡ or blow-by | Requiring high-flow nasal cannula, ‡ facemask, nonrebreather mask, or Venturi mask | Requiring positive pressure (e.g., CPAP, BiPAP, intubation and mechanical ventilation) |

From [Lee 2019](#).

Abbreviations: ASTCT: American Society for Transplantation and Cellular Therapy; BiPAP: bilevel positive airway pressure; CPAP: continuous positive airway pressure; CRS: cytokine release syndrome; NCI-CTCAE: National Cancer Institute Common Terminology Criteria for Adverse Events.

Organ toxicities associated with CRS may be graded according to NCI-CTCAE v5.0 but they do not influence CRS grading.

\* Fever is defined as temperature  $\geq 38^{\circ}\text{C}$  not attributable to any other cause. In patients who have CRS then receive antipyretic or anti-cytokine therapy such as tocilizumab or steroids, fever is no longer required to grade subsequent CRS severity. In this case, CRS grading is driven by hypotension and/or hypoxia.

† CRS grade is determined by the more severe event: hypotension or hypoxia not attributable to any other cause. For example, a patient with temperature of  $39.5^{\circ}\text{C}$ , hypotension requiring 1 vasopressor, and hypoxia requiring low-flow nasal cannula is classified as Grade 3 CRS.

‡ Low-flow nasal cannula is defined as oxygen delivered at  $\leq 6$  L/min. Low flow also includes blow-by oxygen delivery, sometimes used in pediatrics. High-flow nasal cannula is defined as oxygen delivered at  $> 6$  L/min.

The most common anticipated potential toxicities resulting from treatment with agenT-797 are outlined in Section 7.4.1 of the protocol. Some of these possible AEs have also been further defined as AEs of special interest (AESI):

- Cytokine release syndrome (CRS) Grade  $\geq 2$  (as per the American Society for Transplantation and Cellular Therapy [ASTCT] Consensus, in Table 3).
- Hypersensitivity or infusion-related reactions Grade  $\geq 2$  (as per NCI CTCAE version 5.0) directly post-administration of agenT-797.
- Acute GVHD any stage as per the national/local/institutional guidelines.
- Immune effector cell-associated neurotoxicity syndrome (ICANS) Grade  $\geq 2$  (as per the ASTCT Consensus).

The following summaries will be generated based on safety analysis set by dose level and overall:

- A summary of the number and percentage of deaths during the study.
- A summary of the number and percentage of patients reporting a serious TEAE by SOC and PT.
- A summary of the number and percentage of patients with AEs leading to discontinuation of study treatment by SOC and PT.
- A summary of the number and percentage of patients with AESIs leading to discontinuation of study treatment by SOC and PT.

A by-subject listing will be provided for the following events:

- Deaths that occurred during the study.
- Serious TEAE.
- AEs leading to discontinuation of study treatment.
- AESIs leading to discontinuation of study treatment.

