**Statistical Methods:****Sample size**

The total sample size is expected to be up to approximately 43 evaluable, treated patients. Since the study uses a 3+3 design and incorporates 3 dose levels, up to 18 patients may be needed in the Dose Escalation study component (Part 1). Up to 15 patients will be enrolled into Cohort 4 to further evaluate safety (Part 2, Expansion).

Refer to the statistical analysis plan (SAP) for details. A matched control may be used to complete the comparative analysis. This will be defined in the SAP.

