| 
 
To assess evidence of improvement and resolution of ARDS following infusion with agenT-797
 
To assess avoidance of multiorgan dysfunction syndrome
 
                                                                 | 
 
Assessment of ventilator-free days
 
Time to extubation
 
Time to intubation in patients with moderate ARDS
 
Vital signs and physical examination findings
 
Lung injury score (LIS): The LIS is a composite 4-point scoring system including the PaO2/FiO2, positive end-expiratory pressure (PEEP), quasi-static respiratory compliance, and the extent of infiltrates determined by imaging
 
Intensive care unit-free days
 
Mean daily sequential organ failure assessment score(s)
 
Supportive interventions used (e.g., use of prone ventilation, paralytics, pulmonary vasodilators, and other interventions affecting oxygenation)
 
All-cause mortality rates within 30 days and at 6 months
 
 |
| 
 
To assess evolution of cytokine release syndrome (CRS)
 
                                                                                                                                                                     | 
 
Change in clinical parameters and biomarkers relevant to CRS (D-dimers, ferritin, C-reactive protein, IL-1, and IL-6)
 
                                                                                                                                                                                                                                                                                                                                                                                                                                                                                                                                                                                                                                                                  |

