## 4. INVESTIGATIONAL PLAN

### 4.1. OVERALL STUDY DESIGN

This is a Phase 1/2 study to evaluate the safety and potential efficacy of agenT-797, an unmodified, allogeneic iNKT cell therapy, in patients with moderate to severe ARDS secondary to SARS-CoV-2 or influenza, either with intubation or at high risk to be intubated, as determined by the Berlin definition ([ARDS 2012](#)).

**Completed:** Part 1 will employ a standard 3+3 dose escalation design of agenT-797. All patients will receive a single infusion of agenT-797. Patients will also receive other treatments and supportive care per discretion of the Principal Investigator. Once the maximum tolerated dose (MTD) of agenT-797 has been cleared in Part 1, an Expansion Cohort will be opened. A Safety Monitoring Committee (SMC) will be established to assess safety and decide on escalation to

next cohort and expansion dose, as well as any protocol modification to include less severe cases.

**Part 2 (Expansion)** of the study will evaluate an additional cohort in up to 15 patients:

- Cohort 4 – patients with moderate to severe ARDS secondary to SARS-CoV-2 or influenza, according to Berlin definition, who are on mechanical intubation

The SMC will continue to review safety.

The number of patients in each cohort is presented in [Table 2](#).

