### **4.5.3. Safety Criteria for Adjustment or Stopping Doses**

Enrollment and treatment will be temporarily stopped if any of the following occur:

- DLT(s) defined as follows: two Grade 4 DLTs or single Grade 4 neurological toxicity or single Grade 3 or higher GVHD as DLT
- Any toxicity that is unexpected, significant, and unacceptable (based on SMC review and discussion), e.g., any occurrence of GVHD Grade 3 or higher
- Any death that occurs within 30 days of agenT-797 administration, except cases reported as related to the primary disease (COVID-19 or influenza)

If any of the above stopping criteria are met, an SMC meeting will occur to review the information and to recommend how to proceed.

The SMC will review any cohort under evaluation as well as the safety of all cohorts. All toxicities, including those outside the 14-day DLT period, will be evaluated. The SMC will make recommendations regarding any changes in study conduct ([Section 8.2](#)).

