- a End-of-Hospitalization is defined as patient discharge from hospital and/or death. If a patient is discharged at Day 30, 30-day Follow-up will be the same as EOH. After discharge, a patient will enter Safety Follow-up period and the patient will be contacted by telephone 3 and 6 months after discharge regarding any SAEs and to confirm survival, as feasible. See [Sections 4.9 and 4.10](#).
- b In case of earlier discharge from the hospital, no visit is expected until 30-Day Follow-up.
- c Performed before infusion of agenT-797 on D1. These samples will be obtained at the time of the routine labs blood draws.
- d A complete examination, as feasible, will be performed at Screening and symptom-directed and medically indicated physical examinations are done thereafter.
- e Vital signs include body temperature, heart rate, respiratory rate, systolic and diastolic blood pressure and are assessed by physician or nurse. On the day of infusion of agenT-797 (D1), measurements will be 15 min prior to infusion, and 15 min, 30 min, 1h, 2h, 3h, and 4h postinfusion.
- f ECG to be performed at Screening, Day 1 predose and EOH, 30-Day Follow-up, and at other times as clinically indicated.
- g Only AEs associated with study procedures and/or leading to withdrawal and all SAEs will be collected prior to study drug infusion. Patients are monitored for toxicities following infusion. All other AEs, SAEs, and AESIs will be collected as per [Section 8](#) and as defined in the Safety Follow-up period ([Section 4.10](#)).
- h Hematology/coagulation/clinical chemistry: Complete blood count with automated and/or manual differential will be collected daily, as feasible. Coagulation: activated partial thromboplastin time and international normalized ratio. Clinical chemistry: includes but not limited to albumin, alkaline phosphatase, alanine aminotransferase, aspartate aminotransferase, blood urea nitrogen, urea, calcium, chloride, C-reactive protein, creatinine, glucose, lactate dehydrogenase, magnesium, phosphate/phosphorus, potassium, sodium, total bilirubin, direct and indirect bilirubin, total protein, and beta-2-microglobulin and will be collected daily, as feasible. All will be collected at EOH and at 30-Day Follow-up.
- i Urinalysis: pH, ketones, specific gravity, bilirubin, protein, blood, and glucose. Will be done at the days indicated and at EOH and at 30-Day Follow-up.

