### 4.5 Analysis Sets

Three subject analysis sets are defined for the study analyses, as follows:

- **The All Subject Analysis Set** will include all patients who have completed informed consent, irrespective of the study treatment administered. This analysis set will be used for the disposition summary and the listing of study populations.
- **The Safety Analysis Set** will include all patients who received agenT-797. This analysis dataset will be used for safety analysis and all listings other than listings of subject disposition and study populations.
- **The Dose-Limiting Toxicity Analysis Set** will include all patients who either experienced a DLT within 28-day observation or completed study treatment and 28-

day observation for DLT without experiencing DLT. The DLT analysis set will be used for the analysis of DLT rates and for determining MTD.

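### Neurotoxicity counts take no account of whether intubated patients could be assessed, so a low or zero count in Cohort 4 may overstate the evidence of no neurotoxicity

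*Combined protocol and SAP*

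**What the plan says.** Neurotoxicity enters the safety plan in three places.

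- **AESI.** SAP 4.11.5 and Protocol 8.1.3 list "Immune effector cell-associated neurotoxicity syndrome (ICANS) Grade" 2 or higher among four AESIs.
- **DLT.** Protocol 8.1.4 makes any at least possibly related neurologic toxicity of Grade 3 or higher a DLT, whatever its duration.
- **Pause trigger.** Protocol 4.5.3 and SAP 3.8 pause enrolment and treatment for "two Grade 4 DLTs or single Grade 4 neurological toxicity", among other triggers.

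The denominators are in SAP 4.5. The Safety Analysis Set "will include all patients who received agenT-797. This analysis dataset will be used for safety analysis". The DLT set takes patients who had a DLT, or who completed treatment and a 28-day observation without one. AE, SAE and DLT summaries are by dose level and overall (SAP 4.11.4 to 4.11.6).

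Cohort 4 consists of patients with moderate to severe ARDS "according to Berlin definition, who are on mechanical intubation" (Protocol 4.1). Its purpose is stated in the synopsis: "Up to 15 patients will be enrolled into Cohort 4 to further evaluate safety". The supportive interventions recorded as a secondary endpoint include "use of prone ventilation, paralytics, pulmonary vasodilators, and other interventions affecting oxygenation" (Protocol 3).

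On detection, the SAP places a brief neurologic examination at screening (4.11.8.1). After that, "symptom-directed and medically indicated physical examinations are done thereafter" (Protocol Table 3, footnote d), within a row marked for daily monitoring. No neurotoxicity or sedation scale is scheduled. The only recurring neurologic item is the Glasgow Coma score inside SOFA, collected daily as needed.

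**The concern.** A neurologic event can be counted only if someone can see it. A patient under neuromuscular blockade or continuous sedation may show no neurologic sign, and an examination prompted by symptoms may then never be prompted. Neither analysis set separates a patient who was examined and had no event from one who could not be examined. Both add to the denominator and neither adds to the numerator.

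The plan does allow for masking elsewhere in the same AESI list. For cytokine release syndrome, both documents drop the fever requirement once antipyretic or anti-cytokine therapy has been given, and they exclude hypotension or hypoxia with another cause. Neurotoxicity has no corresponding rule.

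At stake is how a low or zero neurologic count is read in the cohort enrolled to evaluate safety further. The same question arises, to a lesser extent, for intubated patients in Cohorts 1 to 3.

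**Working it through.** The documents state no expected neurotoxicity rate, no precision target and no share of patients paralysed or sedated. There is therefore no plan figure to reproduce. The check has two parts.

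**1. How an unassessable patient is counted**

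| Output | Denominator | Condition on assessability | Patient unassessable throughout |
|---|---|---|---|
| Neurologic AEs and ICANS in the AE and SAE tables (SAP 4.11.4, 4.11.5) | Safety set: all treated | None | Counted as event-free |
| Neurologic DLT (SAP 4.11.6) | DLT set | None; completed observation is enough | Counted as event-free |
| ICANS as an AESI (SAP 4.11.5) | Safety set | None | Not tabulated unless it led to discontinuation |
| Pause trigger (Protocol 4.5.3) | None; it is a count | Not applicable | Adds nothing to the count |

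The third row is a gap of its own. The only AESI table and listing cover AESIs leading to discontinuation of study treatment. Treatment is one infusion, so ICANS arising after it would appear only in the general AE and SAE outputs.

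**2. What the denominator does to a zero count**

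Inputs: 15 is the planned maximum for Cohort 4 (Protocol Table 2). The assessable numbers 10 and 6 are assumptions. Wilson is the interval named in SAP 4.2.

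For 0 events in n patients, the two-sided 95% Wilson upper limit is z²/(n + z²), with z = 1.96 and z² = 3.8415.

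- n = 15: 3.8415/18.8415 = 20.4%
- n = 10: 3.8415/13.8415 = 27.8%
- n = 6: 3.8415/9.8415 = 39.0%

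If only assessable patients can show an event, the chance of seeing none is (1 − p)ⁿ, where p is the true rate. The rates below are assumptions.

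| Assumed true rate | n = 15 | n = 10 | n = 6 |
|---|---|---|---|
| 5% | 46% | 60% | 74% |
| 10% | 21% | 35% | 53% |
| 20% | 4% | 11% | 26% |

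**Pooling.** Cohorts 3 and 4 both receive 1000 × 10⁶ cells, and tables are by dose level. Cohort 3 is planned at 6 or more, so with Cohort 4 full the pooled group has at least 6 + 15 = 21 patients. The Wilson upper limit for 0 of 21 is 3.8415/24.8415 = 15.5%. A loss of assessability confined to Cohort 4 would not be visible in that row.

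**The case against.** The strongest reply is that the plan neither computes nor claims what the illustration shows. Much of that reply stands.

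- **No 0/15 with an interval is planned.** Safety summaries are numbers and percentages, confidence intervals are specified for efficacy-type estimates, and no table for Cohort 4 alone is specified. The limits above show how strong the evidence would be; they are not planned outputs.
- **A reader might infer that intubated patients cannot show neurotoxicity.** The documents do not support that. They never mention sedation, they name paralytics only as an example, and they give no share or duration. Reduced or uncertain detection is as far as the text goes.
- **A reader might infer that every neurologic count is over all treated patients.** That holds only for the AE and SAE summaries. DLTs use the DLT set.
- **A reader might infer that absence of events will be reported as safety.** No section says so. The SAP calls its analyses descriptive, and Cohort 4 is to evaluate safety further, not to establish it.
- **A reader might expect an SAP flag to repair the pause trigger.** It cannot. The trigger is a count applied during conduct. The SMC also reviews safety on an ongoing basis, and Protocol 4.12 gives other grounds for stopping enrolment.
- **Detection does not end with the DLT window.** Treatment-emergent events have no such limit, and AESIs are followed whatever the study day. A patient who becomes assessable later can still contribute an event to the AE tables.
- **Percentages among assessable patients are open to selection.** Paralysis or sedation after infusion is a post-treatment state, and toxicity could itself prolong it. Such a percentage can be supplementary only.

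None of this supplies an assessability rule. The SMC weighs concomitant medication when judging a DLT, but only for a toxicity that has already been noticed.

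**Conclusion.** The gap is real but limited. Neurologic AEs, ICANS and neurologic DLTs are summarised without regard to assessability, in a plan whose expansion cohort is entirely intubated. A patient who could not be assessed in the relevant window counts as event-free, so a zero or low count may overstate the evidence of no neurotoxicity.

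The size depends on a share that the documents do not give. If every Cohort 4 patient is assessable at some point, no patient falls into the never-assessable group. If 10 or 6 of 15 are, the upper limit compatible with zero events is 28% or 39% instead of 20%.

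This is a demonstrated omission in reporting, not a demonstrated bias in the primary safety result. It is worth correcting because the correction is cheap and hides nothing.

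**What to change.** In SAP 4.11.5 and 4.11.6:

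1. Keep the safety-set and DLT-set counts as primary.
2. Beside them, show for each cohort, with Cohort 4 separate from Cohort 3: patients with a neurologic event or ICANS; patients assessable; and event-free patients who were never assessable.
3. Derive assessability from the dated medication and procedure records, with Glasgow scores where recorded. Never assessable means no day in the window free of paralysis or continuous sedation. Always count a patient with an event as assessable, so that the numerator lies inside the denominator. State the window used for each table.
4. Give the percentage and Wilson 95% interval among assessable patients as a supplementary figure only. Qualify any statement of no neurotoxicity by the never-assessable count.
5. Tabulate and list all AESIs, not only those leading to discontinuation.
6. Before deriving the flag, reconcile the DLT window, which is 14 days in Protocol 4.5.1 and 8.1.4 and SAP 3.6 but 28 days in the DLT set of SAP 4.5.

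The cost is SAP wording, one derived flag and one added table, with no new visits. Medications and procedures are already collected continuously, and the SAP already uses medication start and stop dates. The downsides are a smaller supplementary denominator, a wider interval and an imperfect flag: sedation depth is not collected, Glasgow scores come only as needed, and some medication dates will be partial. The rule is also lenient, because one clear day makes a patient assessable, so the never-assessable count is a minimum for lost observation.

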#### **5.1.2. Infusion of agenT-797**

After thawing and dilution (see [Section 6.4.1](#)), agenT-797 will be administered as a single intravenous (IV) infusion of allogeneic iNKT cells over 10 to 30 minutes. Patients will be monitored in the clinic for at least 4 hours postinfusion.

In the event of reactions/toxicities during the infusion, the infusion rate may be modified, but the total infusion time should not exceed 60 minutes.

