### 8.1.3. AESIs

AESIs are defined as the following events:

- CRS Grade  $\geq 2$  (ASTCT consensus; [Lee 2019](#)). See [Section 5.4.1.1](#)
- Hypersensitivity or infusion-related reactions Grade  $\geq 2$  (as per NCI-CTCAE v5.0) during and up to 24 hours following administration of agenT-797
- Acute GVHD, any stage, as per national/local/institutional guidelines
- Immune effector cell-associated neurotoxicity syndrome Grade  $\geq 2$  (ASTCT consensus; [Lee 2019](#))

The AESI should be entered on the AE CRF and reported using the procedures detailed in Recording and Reporting of AEs in [Section 8.1.5](#). Even if the AESI does not meet the SAE criteria, it must still be reported using the SAE form and in an expedited manner but should be noted as non-serious on the SAE form and the AE CRF.

AESIs both non-serious and serious identified in this protocol will be followed from the onset through resolution/outcome, regardless of day of study when identified.

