## **4.10 Treatment Exposure / Compliance**

### **4.10.1 Treatment Exposure**

AgenT-797 will be administered as a single intravenous infusion of allogeneic iNKT cells over 10 to 30 minutes on Day 1. The extent of the exposure to agenT-797 will be summarized and presented based on the safety analysis set, by dose level and overall. The summary will include:

- Duration of agenT-797 administration, defined as the number of minutes between the administration start time and the end time
- Calculated dose level
- Actual dose level

A by-subject listing of exposure data will be provided.

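### SAP 4.11.5 plans no incidence summary of adverse events of special interest: its only AESI table and listing require discontinuation of a single short infusion

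*Combined protocol and SAP*

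**What the plan says.** SAP 4.11.5 names four AESI types: CRS of Grade 2 or more on the ASTCT scale, hypersensitivity or infusion-related reactions of CTCAE Grade 2 or more, acute GVHD of any stage, and ICANS of Grade 2 or more on the ASTCT scale. It then plans one AESI table, "A summary of the number and percentage of patients with AESIs leading to discontinuation of study treatment by SOC and PT", and one AESI listing by subject, of "AESIs leading to discontinuation of study treatment". No other output in the SAP carries the AESI label.

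On exposure, SAP 4.10.1 states: "AgenT-797 will be administered as a single intravenous infusion of allogeneic iNKT cells over 10 to 30 minutes on Day 1". Protocol 5.1.2 allows the rate to be changed if a reaction occurs, but "the total infusion time should not exceed 60 minutes". On timing, SAP 4.11.5 says: "The onset of CRS can typically occur between 24 hours and 14 days after the completion of T cell administration".

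The two documents differ on when an infusion reaction counts as an AESI. Protocol 8.1.3 has "during and up to 24 hours following administration of agenT-797"; SAP 4.11.5 has "directly post-administration of agenT-797".

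Protocol 8.1.3 also requires AESIs to be entered on the adverse event CRF, and protocol 8.1.6 requires adverse events to be categorised as AESIs where that applies.

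**The concern.** The condition on discontinuation makes sense for a drug given repeatedly, where an event in one cycle can prevent the next. Here there is nothing left to discontinue once the bag has run in. The table therefore selects on something that almost none of these events can cause, and a zero in it would reflect the filter rather than the safety of the product.

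Safety and tolerability are the sole primary objective, and AESIs are the toxicities that the sponsor singled out for an allogeneic cell product. The protocol asks sites to report them within 24 hours even when non-serious (8.1.10) and to follow them to outcome (8.1.3). A clinical study report built from the SAP would then contain no table saying how many patients had each one.

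**Working it through.** No rate, sample size or power figure is stated for AESIs, so there is nothing numerical to reproduce. The check has three steps: can an AESI meet the filter, what do the other planned outputs supply, and what remains missing?

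**1. Can an AESI lead to discontinuation of the infusion?**

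- Longest infusion: 60 minutes (protocol 5.1.2). Earliest typical CRS onset: 24 hours after completion (SAP 4.11.5). Counted from the start of a 60-minute infusion, that is 1 h + 24 h = 25 h. For a 10-minute infusion it is 24 h 10 min. In both cases onset falls 24 hours after the last moment at which the infusion could have been stopped.
- Acute GVHD and ICANS: neither definition gives an onset window. They meet the filter only if they arise and are recognised within the same 60 minutes.
- Hypersensitivity or infusion reaction: under the protocol wording a reaction during the infusion is an AESI and could stop it. Under the SAP wording read literally, the AESI begins after administration and cannot stop it.

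In the typical case, then, one of the four types can enter the table under the protocol definition and none under a literal reading of the SAP definition.

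**2. What do the other outputs supply?**

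| Planned output | Independent of discontinuation? | What it gives on AESIs |
|---|---|---|
| SAP 4.11.4: tables of AEs, TEAEs and related TEAEs, and TEAEs by severity and by causality | Yes | Patients per SOC and preferred term, per dose level and pooled |
| SAP 4.11.4: listing of every AE | Yes | Each event with dates, severity, action taken, outcome and causality; no AESI flag among the stated fields |
| SAP 4.11.5: serious TEAE table and listing | Yes | AESIs that are also serious |
| SAP 4.11.6: DLT summary | Yes | Patients with any DLT, not broken down by type |
| SAP Table 2 and 4.11.2.3: CRS evolution | Yes | Listings and plots of parameters and biomarkers; no count of patients with CRS |

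**3. What remains missing?**

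- *Grade threshold.* The severity scale stated for the AE tables is CTCAE v5.0. The CRS and ICANS AESIs are defined by ASTCT grade. No table is specified on that scale, and none is specified by GVHD stage.
- *Grouping.* A table by preferred term does not combine terms. If infusion reactions or neurotoxicity are coded to several terms, no row gives the number of patients with at least one such event.
- *DLTs are narrower than AESIs.* Under protocol 8.1.4, CRS is a DLT when it is new Grade 3 beyond 72 hours, new Grade 4, or a worsening of baseline Grade 2 or 3 CRS within 4 hours of infusion, and at least possibly related. New Grade 2 CRS is an AESI and not a DLT under that CRS criterion. Acute GVHD below Grade 3 is a DLT only under the stated Grade 2 steroid-response conditions, whereas any stage is an AESI.

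**The case against.** The strongest reply is that nothing is hidden. AESIs go on the AE CRF, so every one should reach the SAP 4.11.4 tables and the listing of all AEs, none of which depends on discontinuation. With up to about 43 patients planned, that listing can be read from end to end. For acute GVHD there is no grade cut to apply, so its preferred-term row already gives the incidence, without the stage. On CRS, SAP 4.11.5 reproduces the ASTCT table for the investigator's use, so the severity entered for CRS may in practice be the ASTCT grade. Finally, the table's title states its condition, and a careful reader would not take it for an incidence table.

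Most of this stands, and it rules out two stronger readings that a reader might infer. One is that rates of CRS, GVHD and neurotoxicity are never produced, or that such events are tabulated only if treatment stopped. SAP 4.11.4 contradicts both. The other is that the AESI table must be zero for CRS by construction. The onset window is described as typical, and protocol 8.1.4 itself provides for worsening of baseline CRS within 4 hours of infusion. Nearly empty is as far as the documents go.

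The reply does not restore what the AESI outputs are for. The SAP does not say which scale the CRS rows of the severity table use, so the reader cannot rely on their being ASTCT grades. Reactions and neurotoxicity are not grouped, and the listing has no stated flag by which to pick AESIs out.

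**Conclusion.** The concern holds as a moderate reporting gap on the primary objective. The one AESI table and one AESI listing are close to uninformative in a single-infusion study, and no other planned output is built on the AESI definitions. The size is best put by type. For CRS and ICANS, incidence at the defining ASTCT grade is not assured. For infusion reactions, and for neurotoxicity coded to several terms, a count of affected patients is not assured. For acute GVHD, only the breakdown by stage is missing.

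A reader might go further and conclude that safety information is lost. The documents do not support that: the events are collected, categorised as AESIs, counted by preferred term and listed.

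The conclusion assumes that discontinuation has its ordinary meaning of stopping the infusion before the full dose, and that events follow the onset pattern the SAP describes. How often reactions or neurotoxicity would be split over several terms cannot be judged from the documents.

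The difference between the two infusion-reaction windows is a separate inconsistency. It matters here because it decides whether a reaction during the infusion is an AESI at all.

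**What to change.** In SAP 4.11.5:

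1. Remove the discontinuation condition from the AESI table and listing.
2. Report, per dose level and pooled, how many patients (n and %) had each AESI type, by maximum grade or stage: ASTCT for CRS and ICANS, CTCAE for hypersensitivity and infusion reactions, local staging for acute GVHD. State which preferred terms or CRF flag define each type.
3. List all AESIs by subject with day of onset, and add an AESI flag to the all-AE listing in SAP 4.11.4.
4. Reconcile the infusion-reaction window between SAP 4.11.5 and protocol 8.1.3, so that one definition drives both collection and analysis.
5. Correct the reference to protocol Section 7.4.1 in the same block; the content it points to is in protocol 5.4.1.

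Confidence intervals are optional. The SAP is descriptive and plans none for its AE tables, and Cohorts 1 and 2 have only 3 to 6 patients each.

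The cost is a wording change, one table shell, one listing and one added field. The protocol already requires AESI categorisation, so no new data collection is called for.
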